### Feasibility and usability assessment

To assess feasibility of tVNS in MCI, VINCI-AD will assess report the number of participants completing assessment across the three sessions. To assess usability of the device, a modified Kettle test has been designed with senior Occupational Therapy colleagues in our institution (see Additional File 3). The Kettle test is a brief, objective assessment of functional skills [44] which has been designed specifically to ascertain the participants’ ability to independently use the NEMOS© tVNS device. At the end of the third session whereby the participants will have been introduced to the NEMOS© tVNS device on three occasions, worn it for two sessions (one active at the cymba conchae and one sham at the earlobe), they will then be presented with the device and asked to set up and use the device as independently as possible. There are 13 objective tasks detailed and each is graded by the assessor from 0 (no assistance required, fully independent) to 4 (fully assisted with this aspect of task performance). Scores on this task range from 0 to 52, with lower scores indicating more independent use of the device and higher scores reflecting more severe difficulty in using the device independently.

Acceptability of the device will be assessed via Likert-based scale questions including if the device felt comfortable, their subjective sense of confidence using the device, would the participant use it again (See Additional File 4).

### Pre-specified exploratory analysis

#### Potential effects of acute tVNS on cognitive performance

VINCI-AD is a safety and feasibility study of tVNS device use in individual with MCI. Exploratory secondary analysis will also assess the potential benefits of acute tVNS on cognitive performance. Cognitive function will be assessed under identical conditions in all participants at all three visits and will encompass assessment of the following:

Face Name Association Task (FNAT): A cross-modal associative memory test [45, 46] hosted on E-PRIME (Psychology Software Tools, Sharpsburg, USA). The participant is shown 30 face-name pairs. After a brief interlude (less than one minute) participants are then shown a combination of faces, some of which have already been displayed. The assessment involves both accurate recognition of recently displayed faces and correct recall of associated names. tVNS has been shown to boost associative memory as assessed by this task in CU older adults [47] but has not been assessed in those with MCI.Sustained Attention to Response Task (SART): A computer based response inhibition task [48] hosted on E-PRIME (Psychology Software Tools, Sharpsburg, USA) This is similar to Go/No-Go or Stop/Signal tasks whereby participants are required to withhold response to a single, infrequent target (the digit 3) presented amongst a background of frequent non-targets (0–2, 4–9) to which the participant does respond by pressing the space key on the computer keyboard.SeaHero Quest ™ the electronic tablet-based app Sea Hero Quest (GLITCHERS © London, UK; University College London, London, UK) will be used whereby participants will be asked to complete 5 levels of increasing complexity of a nautical-themed navigation task designed to assess speed and accuracy of navigating a boat to a map target [49, 50].Language assessments will include list learning, semantic fluency, list recall and list recognition assessments adapted from RBANS battery as tVNS has demonstrated benefits in these domains in both healthy [26, 51] and clinical populations [11, 12].Working memory will be assessed via digit span forward and backward which will be undertaken as part of the adapted RBANS battery.

Participants will wear the portable NIRS analysis device during all cognitive tasks so that the TSI may be measured continuously during cognitive tasks at baseline, during active and during sham stimulation.

#### Potential effects of acute tVNS on heart rate variability

HRV assessment will be undertaken using a 3 – lead continuous ECG measure via the Finapres© device. HRV analysis will be undertaken during five minutes of rest pre-active stand or any cognitive assessments. Various HRV measures will be taken, however specifically the root mean square of successive R-R interval differences (RMSSD) is of interest as it has been shown to be most highly correlated with cognition and executive function on metanalysis [52].

#### Potential effects of acute tVNS on inflammatory markers

Aseptic peripheral venepuncture will be performed 50–60 min following neurocardiovascular and cognitive assessments have been undertaken at all three study visits. 7-10ml of blood will be taken in EDTA Vaccutainers, centrifuged at 3,400 rpm for 10 min at 18 °C and supernatant stored in 1ml aliquots at -80 °C for later analysis. A custom-battery of 12 cytokines and chemokines will be analysed using the MesoScale Discovery (MSD) V-PLEX Electrochemoluminescence assay according to standard protocols and includes: IL-1RA, IL-6, IL-8, IL-10, IL-17 A, MIP-1 β, IL12p70, IP-10, TNF- α, MCP-1, Eotaxin, IFN- γ based on known associations with MCI in international literature [53, 54]. Please see Fig. 2 for study visit schedules including minutes of stimulation, methods of assessment and timelines.

**Fig. 2 Fig2:**
[figure not shown]
Study visit schedule and design

### Randomisation

Patients who provide informed consent to participate and who fulfil eligibility criteria will be enrolled into the study. Initial visit (visit 1) involves baseline assessments of neurocardiovascular, cognitive, and inflammatory status. Participants are then randomised to either active or sham stimulation condition at the following visit and then to the alternate condition at the final visit. Participants are blinded to the active or sham stimulation condition but study researchers are not (i.e. single-blinded). Please see Fig. 1 for randomisation strategy.

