**Design:**

VINCI-AD is an investigator-led, single-site, single-blind, sham-controlled crossover pilot study which aims to assess the safety and feasibility of tVNS in 40 participants with amnestic MCI. All participants will attend for three consecutive study visits during which they will be randomised to receive no stimulation (baseline), active tVNS stimulation (stimulation at cymba conchae of left ear) or sham tVNS stimulation (at earlobe). Safety will be primarily assessed by ascertainment of adverse events. Further safety assessment will examine the impact of acute tVNS on subjective (orthostatic symptoms), peripheral (finometry-based blood pressure) and central (assessed via Near Infrared Spectroscopy [NIRS]) haemodynamic responses to active stand. Feasibility will be determined using a custom-designed occupational assessment of device usability. Exploratory secondary analysis in VINCI-AD will examine the potential impact of acute tVNS on associative memory, spatial memory and inhibitory control to inform sample size estimates for future trials of tVNS in older adults with MCI.

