### Intervention

Participants will receive active and sham stimulation with the NEMOS © CerboMed tVNS device. Two small electrodes emit a low-voltage electric signal which permeates the skin. When the electrodes are placed at the cymba conchae of the ear, stimulation actives the afferent branch of the VN that innervates the skin of the ear (Arnold’s nerve). The electric signal consists of an 8 Hz frequency wave with participant-selected amplitudes ranging from 0.1 mA to 5 mA depending on their sensory threshold, the signal cycles of 200 ns and comes in 30 s on – 30 s off bursts. For the sham condition the electrode is placed on the earlobe which is free of vagus innervation. For the active condition it is placed on the cymba conchae of the left ear. At each stimulation study visit the device is explained to the participant and then fitted by the study researcher. Participants are given oral and written instructions at each stimulation study visit regarding how to set up and fit the device in their ear.

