### Safety and tolerability of tVNS in MCI

The risk associated with use of the NEMOS © Cerbomed tVNS device is minimal as published data of the safety profile shows minimal adverse events. The most common adverse events reported include local skin tingling, burning, redness, itching, tinnitus or headache which occur in up to 18% of participants, and tends to resolve quickly after discontinuation of the use of the device [42]. Due to the theoretical risk of increasing cardiac vagal-mediated bradycardias or hypotensive episodes by stimulating the right VN, participants will have stimulation of the left ear only.

During the active and sham stimulation conditions, safety will be recorded by completion of the following:

Contemporaneous recording of any adverse events reported by participants whilst undergoing either active or sham stimulation.Likert-Based Questionnaires (See Additional File 2) will assess for established side effects previously reported with tVNS: pain, skin discomfort, tingling, headache and tinnitus. These will be administered both during active and sham stimulation.Detailed assessment of subjective (OH symptoms including faintness, light-headedness), peripheral (beat-to-beat blood pressure) and central (TSI) haemodynamic responses to active stand.
Briefly, participants will undergo active stand from supine to standing. After lying supine for 5 min, participants will be asked to stand as fast as they can. Beat-to-beat blood pressure and heart rate responses (assessed via the Finapres© NOVA) will be monitored during active stand and for three minutes after. To standardise assessments, all assessments are all taken at the same time each day, and all routine medications are taken as usual each morning. OH is defined by consensus as a sustained reduction of systolic blood pressure (SBP) of at least 20 mmHg or diastolic blood pressure (DBP) of 10 mmHg within 3 min of standing [43].
During active stand, cerebral oxygenation (TSI) will be estimated using NIRS-based analysis software. TSI analysis will be undertaken using the PortaLite OxySoft© NIRS device (PortaLite, Artinis Medical Systems B.V., Elst, The Netherlands) and the light emitting diode will be placed on clean skin on the right forehead, devoid of moisture or oil, and secured with a black headband. TSI readings are transferred via Bluetooth in real-time and will give an approximation of tissue oxygenation during rest, active stand, and all cognitive assessments.

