### Statistical analysis

VINCI-AD will assess the safety and feasibility of tVNS in older adults with MCI. All participants will be included in final analysis in an “intention-to-treat” fashion. Statistical analysis will be conducted using MATLAB (The MathWorks, Inc., Natick, MA, USA), SPSS (IBM SPSS Statistics for Windows, Armonk, NY: IBM Corp) and GraphPad Prism (GraphPad Software, Inc., San Diego, CA, USA). We anticipate that TSI analysis will require cleaning to remove “noisy” channels i.e. removing large spikes (changes in oxy-Hb larger than 0.5 mM/mm in amplitude); noisy channels will be excluded from analyses and data analyses will utilise software Platform for Optical Topography Analysis Tools [56] with a bandpass filter with cut-off frequencies of 0.01–0.8 Hz to remove instrumental or physiological noise [57].

In the first instance, descriptive statistics will be described for the cohort, reported as means (with standard deviations) or medians (with inter-quartile ranges) and proportions (percentages) as appropriate.

The primary aim of the current study is to assess the safety and feasibility of tVNS in MCI. To assess safety, a chi-square test will compare the number of adverse events reported during the active vs. sham condition. Further safety assessment will elicit symptoms experienced during active stand (using a chi-square statistic), peripheral (beat-to-beat blood pressure response to orthostasis – using mixed-effects linear regression with study condition as the independent variable, with random intercepts for study participant) and central (TSI – also assessed using a linear mixed-effects model). Feasibility will be reported via recruitment rates, successful enrolment, and study completion in proportions and percentages. Tolerability will be assessed using Likert scales, which will be compared between active and sham conditions using paired between-condition statistics (t-test if normally distributed or non-parametric equivalent). Descriptive statistics will be used to report acceptability using the modified Kettle test.

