### Data collection and data management

Data will be collected by research personnel, all of which have been trained in the principles of good clinical practice. Experimental data is pseudo-anonymised then recorded and managed on a secure encrypted local database. Filled-out data collection files will be transferred to the secure database by one researcher. Digitalised data are stored for 5 years after study end. For each participant, a physical Case Report Form, containing all physical source material, will be kept in a secure and locked location for 5 years. Serum samples will be stored at the research laboratory for a maximum of 5 years. Samples will be anonymised and labelled with subject randomisation ID and date of sample collection.

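### The adverse-event record and active-stand symptoms, both compared active versus sham, appear to be taken by staff who know the condition

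*Protocol article*

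**What the plan says.** The Randomisation section of the protocol article states: "Participants are blinded to the active or sham stimulation condition but study researchers are not (i.e. single-blinded". Single-blinding is also declared in the abstract and under Study design.

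Under Intervention, the active electrode goes on the cymba conchae and the sham electrode on the earlobe. The same section says: "At each stimulation study visit the device is explained to the participant and then fitted by the study researcher". Under Data collection and data management: "Data will be collected by research personnel, all of which have been trained in the principles of good clinical practice". No separate blinded assessor is named.

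The abstract's Design paragraph gives the lead safety measure: "Safety will be primarily assessed by ascertainment of adverse events". The section on safety and tolerability describes its capture as "Contemporaneous recording of any adverse events reported by participants whilst undergoing either active or sham stimulation". It adds Likert questionnaires on pain, skin discomfort, tingling, headache and tinnitus: "These will be administered both during active and sham stimulation". It also covers faintness and light-headedness at active stand.

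The Statistical analysis section says: "To assess safety, a chi-square test will compare the number of adverse events reported during the active vs. sham condition". It continues: "Further safety assessment will elicit symptoms experienced during active stand", again with a chi-square statistic. Likert scores are compared within person, as a measure of tolerability.

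**The concern.** The lead safety result is a difference between two conditions, and the people who appear to record the events know which condition is running. The side effects the article expects (tingling, burning, redness, itching, tinnitus, headache) are mild, quick to resolve and mostly subjective. How far a participant is prompted, and whether a passing sensation is written down, can depend on the person taking the record. Blinding the participant does not cover that step.

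A difference in logging could run either way. Active-session sensations might be passed over as expected, which makes the device look safer, or active sessions might be watched more closely, which makes it look worse. Neither a larger sample nor another test removes a bias introduced at collection.

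**Working it through.** **Step 1. Who takes the record.** No single sentence names the recorder, so this is an inference from four places:
- Randomisation: study researchers are not blinded, and no exception is given.
- Intervention: the study researcher fits the electrode, so sees the site at each stimulation visit.
- Data collection and data management: research personnel collect the data.
- Safety and tolerability: adverse events are recorded while stimulation is under way.

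Together these indicate that the record is taken by staff who know the condition.

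**Step 2. Which measures are exposed.**
- *Adverse-event record:* the report comes from a blinded participant; prompting and logging are exposed.
- *Active-stand symptoms:* elicited, so the questioning itself is exposed.
- *Likert items:* named side effects asked about in both conditions, so less exposed. They may be self-completed; Additional File 2 is not shown.
- *Beat-to-beat blood pressure and tissue saturation index:* instrument readings, less exposed.

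**Step 3. Illustration of size.** The article gives no figure to reproduce here: the sample of 40 rests on precedent, without alpha or power. Inputs from the article are n = 40 (Sample size) and up to 18% of participants with an event (Safety and tolerability). Assumptions are that 18% applies equally to both conditions, and that active-session events are logged at a share r of the sham-session rate.

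Expected participants with an event per condition: 40 × 0.18 = 7.2.

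Recorded active rate = 0.18 × r. False difference = 0.18 × (1 − r). In participants = 40 × 0.18 × (1 − r).

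| r | Recorded active rate | False difference | Participants |
|---|---|---|---|
| 0.9 | 16.2% | 1.8 points | 0.72 |
| 0.8 | 14.4% | 3.6 points | 1.44 |
| 0.5 | 9.0% | 9.0 points | 3.6 |

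**Step 4. Effect on the test.** This is an exact binomial enumeration of an uncorrected chi-square test with 40 sessions per condition. The two-sided 5% level is assumed, and within-person pairing is ignored. With equal true rates, the rejection probability is:

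| True rate | r = 1 | r = 0.9 | r = 0.75 | r = 0.5 |
|---|---|---|---|---|
| 18% | 5.2% | 5.7% | 8.8% | 22.7% |
| 30% | 4.8% | 5.9% | 11.7% | 36.6% |

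Masking is the reverse case. Suppose the true rates were 30% active and 18% sham; the test would reject about 24% of the time. If only 60% of active-session events were logged, the recorded active rate would be 0.30 × 0.60 = 18%, equal to sham, and rejection would fall to about 5%.

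**The case against.** The strongest case on the other side has five parts.

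- *Participants are the source.* The article describes adverse events as reported by participants, who are blinded, and says any such event is recorded in both conditions. Eliciting is mentioned only for active-stand symptoms. A reader might infer that staff elicit all adverse events, or have discretion to dismiss some; no passage says so. This stands, and it narrows the point to prompting and logging.
- *Some wording is already fixed.* The Likert items name tingling, headache and tinnitus, and skin discomfort plausibly covers burning, redness and itching. A reader might infer that nothing standardises the questions; that is not supported. However, the Likert scores serve the tolerability comparison, while the chi-square test uses the separate event record.
- *Material is not visible.* Additional File 2 and the visit-schedule figure are not shown, and an article may leave question scripts to fuller documents. This stands for the detail of the forms. It does not change the stated rule that researchers are unblinded.
- *The design is openly single-blind, and whoever fits the device must know the site.* True, so there is no contradiction in the plan. But fitting the electrode requires knowledge of the site; capturing symptoms does not.
- *The logging shares have no source.* True. At 90% logging and an 18% rate, false rejection moves only from 5.2% to 5.7%.

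**Conclusion.** The point holds as a limited design weakness. The adverse-event record and the active-stand symptoms appear to be taken by staff who know the condition, and no visible passage offsets this for those two measures. The Discussion credits the baseline and sham arms with controlling unblinding bias but does not list unblinded recording among the limitations.

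This is a risk of bias. A reader might infer that the safety result is biased, or biased towards showing the device as safe; the document supports neither its presence nor a direction. The illustration runs from negligible (0.7 participants at 90% logging) to material (3.6 participants at 50%). It rests on assumed logging shares, on applying an upper figure of 18% equally to both conditions and, for the rejection probabilities, on ignoring pairing. That unblinded staff keep the record is inferred from several sections together. The case for change is that a less exposed method is cheap.

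**What to change.** 1. **Safety and tolerability section.** Have participants complete a fixed checklist of the expected side effects and active-stand symptoms at the same set times in both conditions, before any open question. Where help is needed, items are read out verbatim.
2. **Statistical analysis section.** Base the active-versus-sham comparison of symptoms and events on those participant-completed items. Report the open adverse-event record alongside, noting that it was taken unblinded.
3. **If an existing team member without the sequence key is available**, that person classifies the log entries before the key is merged. Entries carry participant code and visit only, with ear location omitted because it could reveal the condition. The article does not identify such a person, so this step is conditional.

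**Cost:** changes of wording, one checklist and a few extra minutes per session; the first two steps need no new visits or staff. Some participants with mild cognitive impairment will need items read aloud, so the researcher's influence is reduced but not removed.

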### Sample size

To establish the safety and feasibility of tVNS in a population of older adults with MCI, VINCI-AD aims to recruit 40 participants for inclusion. This sample size is based on previous literature which investigated the effects of tVNS in healthy young adults [19–21, 23, 55] and also CU older adults [47]. Potential effect sizes from the results of this feasibility study will inform an accurate power calculation for future definitive trials.

### Statistical analysis

VINCI-AD will assess the safety and feasibility of tVNS in older adults with MCI. All participants will be included in final analysis in an “intention-to-treat” fashion. Statistical analysis will be conducted using MATLAB (The MathWorks, Inc., Natick, MA, USA), SPSS (IBM SPSS Statistics for Windows, Armonk, NY: IBM Corp) and GraphPad Prism (GraphPad Software, Inc., San Diego, CA, USA). We anticipate that TSI analysis will require cleaning to remove “noisy” channels i.e. removing large spikes (changes in oxy-Hb larger than 0.5 mM/mm in amplitude); noisy channels will be excluded from analyses and data analyses will utilise software Platform for Optical Topography Analysis Tools [56] with a bandpass filter with cut-off frequencies of 0.01–0.8 Hz to remove instrumental or physiological noise [57].

In the first instance, descriptive statistics will be described for the cohort, reported as means (with standard deviations) or medians (with inter-quartile ranges) and proportions (percentages) as appropriate.

The primary aim of the current study is to assess the safety and feasibility of tVNS in MCI. To assess safety, a chi-square test will compare the number of adverse events reported during the active vs. sham condition. Further safety assessment will elicit symptoms experienced during active stand (using a chi-square statistic), peripheral (beat-to-beat blood pressure response to orthostasis – using mixed-effects linear regression with study condition as the independent variable, with random intercepts for study participant) and central (TSI – also assessed using a linear mixed-effects model). Feasibility will be reported via recruitment rates, successful enrolment, and study completion in proportions and percentages. Tolerability will be assessed using Likert scales, which will be compared between active and sham conditions using paired between-condition statistics (t-test if normally distributed or non-parametric equivalent). Descriptive statistics will be used to report acceptability using the modified Kettle test.

Exploratory secondary aims of this study (cognitive testing, HRV analysis, inflammatory responses) will be analysed using a repeated three – way analysis of variance (ANOVA) if parametric or Kruskal-Wallis test if non-parametric analysis required, with Bonferroni corrections for multiple comparisons. We will explore the effects of concentrations of pro-inflammatory plasma cytokines on cognitive and neurocardiovascular characteristics. Missing data will be handled by applicable statistical methods including multiple imputation.

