Oxygenation of cerebral tissue can be noninvasively measures using tools such as NIRS devices. NIRS devices project near-infrared light into underlying tissue (such as cerebral cortical tissue) and measures the backscatter of this light using detectors. Based on the amount of backscatter, the concentration of oxygenated haemoglobin and deoxygenated haemoglobin can be determined and from this information the Tissue Saturation Index (TSI; a measure of tissue oxygenation) can be determined [35]. The TSI has emerged as an objective surrogate marker of cerebral perfusion, suitable for clinical testing of dynamic cerebrovascular hemodynamics during standing [36] and has been evaluated as a marker of oxygenation during tVNS and cognitive testing as well [37]. There is a known age-related reduction in resting-state TSI in the prefrontal cortex in older adults [38] and persons with MCI have lower resting state TSI levels compared to healthy controls [39, 40]. Whether frontal TSI could be augmented by tVNS in a population with MCI remains to be explored.

The Vagus Nerve Stimulation in Mild Cognitive Impairment (VINCI-AD) study will examine the use of an easy-to-use, tVNS device in MCI. VINCI-AD will determine the safety (adverse events ascertainment, peripheral and central haemodynamic responses to active stand) and feasibility of tVNS as a potential treatment in older adults with MCI. Pre-specified exploratory secondary analysis will assess the impact of acute tVNS on cognitive function (namely associative memory, spatial memory, inhibitory control, language and working memory) to provide potential effect size estimates to inform future clinical trials of tVNS in MCI.

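### The 0.01–0.8 Hz bandpass set for TSI analysis removes the TSI level and most of a fall sustained through the stand, so mean-level and sustained-response summaries of TSI could reassure falsely

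*Protocol article*

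**What the plan says.** The Statistical analysis section introduces signal processing with "We anticipate that TSI analysis will require cleaning to remove" noisy channels. The same sentence ends "with a bandpass filter with cut-off frequencies of 0.01–0.8 Hz to remove instrumental or physiological noise". It does not separate the active stand from the cognitive tasks, and it does not mention restoring the baseline level after filtering.

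The section on safety and tolerability lists "central (TSI) haemodynamic responses to active stand" among the safety assessments. The manoeuvre is described as "After lying supine for 5 min, participants will be asked to stand as fast as they can". Blood pressure and heart rate "will be monitored during active stand and for three minutes after"; no separate window is given for TSI. Table 1 places the active stand with TSI under the primary safety outcome. The analysis of this measure is given only as "central (TSI – also assessed using a linear mixed-effects model", without naming the TSI summary that enters the model.

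Elsewhere TSI is treated as a level of tissue oxygenation. The Background cites lower resting TSI levels in MCI and adds: "Whether frontal TSI could be augmented by tVNS in a population with MCI remains to be explored". In the exploratory part, participants wear the device "so that the TSI may be measured continuously during cognitive tasks at baseline, during active and during sham stimulation".

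**The concern.** TSI is a saturation level. The natural questions are whether it falls on standing, how far, for how long, and whether it is higher or lower under active stimulation than under sham or at baseline. A bandpass starting at 0.01 Hz discards what changes more slowly than about once in 100 s, including the mean. Two records with different true levels then look alike, and a fall that persists for three minutes is largely filtered out.

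The error runs in an unhelpful direction. If active stimulation lowered cerebral oxygenation throughout standing, a mixed model on the mean of the filtered trace could show little or no difference between conditions, and the pilot could report that as reassurance. A tonic rise in frontal TSI during cognitive testing, which the Background raises as an open question, would be lost in the same way.

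**Working it through.** **Inputs from the protocol article.** Filter band 0.01 to 0.8 Hz (Statistical analysis). Supine period 5 min = 300 s, and stand observation 3 min = 180 s (Safety and tolerability). The 3 minutes are stated for blood pressure and heart rate; I assume the same for TSI. Stimulation is 30 s on, 30 s off (Intervention).

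**Assumptions.** Sampling at 10 Hz; resting TSI 65%; a 5-point step fall at standing; Butterworth bandpass of orders 1 to 5, run causally (single pass) or zero-phase (forward and backward), with an FFT brick-wall filter as a further variant. The filters are linear with zero gain at 0 Hz, so the retained percentages depend on neither the level nor the size of the fall. The article gives no processed result to reproduce.

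**Step 1: time scale of the lower edge.** Period 1/0.01 = 100 s. First-order time constant 1/(2π × 0.01) = 15.9 s. A 180 s period corresponds to 1/180 = 0.0056 Hz, below the edge.

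**Step 2: level.** Gain at 0 Hz is 0. Traces that are identical except for a resting level of 65% or 60% gave the same filtered output (orders 1 and 3, causal and zero-phase; largest difference below 1e-12). A constant difference in level between conditions is removed completely.

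**Step 3: fall held for 180 s.** Percentage kept = 100 × (filtered supine mean − filtered mean in the stand window) / true fall.

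| Filter | 0–180 s, vs last 60 s supine | 0–180 s, vs whole supine | 60–180 s, vs last 60 s supine |
|---|---|---|---|
| Order 1, causal | 8.7% | 8.7% | 0.3% |
| Order 1, zero-phase | 17.2% | 7.0% | 13.0% |
| Order 2, causal | 0.0% | 0.0% | −0.5% |
| Order 2, zero-phase | 13.2% | 4.9% | 9.7% |
| Order 4, causal | 0.0% | 0.0% | 1.5% |
| Order 4, zero-phase | 11.5% | 4.6% | 8.6% |

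Orders 3 and 5 and the FFT filter (12.3% for 0–180 s) fall in the same range. Across all variants the 3-minute mean keeps 0 to 17%, so 100 − 17 = 83% up to 100% is lost. Causal filters of order 2 or more also overshoot: within the first 60 s, window means reach up to about 32% of the fall in the wrong direction.

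**Step 4: fall developing gradually over the 180 s.** The mean of the last 30 s keeps 0 to 10% (orders 1 to 3).

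**Step 5: what survives.**
- Early nadir of a step, first 30 s: about 50 to 65% of the fall (zero-phase, depending on supine reference) or 96 to 103% (causal).
- Dip recovered by 30 s: 49 to 76% of its depth (orders 1 to 3).
- Response locked to the stimulation cycle: 1/(30 + 30) = 0.0167 Hz, inside the band. For orders 1 to 4 the gain there is 0.86 to 0.99 single pass and 0.74 to 0.99 zero-phase.

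**Step 6: low-pass only at 0.8 Hz.** Gain at 0 Hz is 1. The level is kept, and a sustained fall is kept in full apart from about the first second after standing.

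**The case against.** The best counter-argument concerns scope. The sentence opens with TSI, but its details (a spike rule in oxy-Hb, exclusion of channels, optical topography software) belong to haemoglobin-channel processing. The authors may have meant the filter for the task recordings only. That is possible, and it is a reason to correct the text: as written, the filter governs TSI analysis generally and the stand is not exempted.

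Second, the harm depends on the summary entered in the mixed model, which is not named. This stands. A reader might infer that filtered data would show no central haemodynamic difference at all. The documents do not support that: a nadir or early-drop summary would still pick up an abrupt fall, and the Background names transient reductions in cerebral perfusion as a concern. The word sustained in the safety section belongs to the blood-pressure definition of orthostatic hypotension, not to TSI.

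Third, a reader might infer that any augmentation during cognitive tasks is hidden. Only a tonic shift is; a cycle-locked response passes. Nor does a flat bound of at least 90% lost hold. Against the last 60 s supine, an order-1 zero-phase filter keeps 13% at 60–180 s and 17% of the 3-minute mean.

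Finally, the Abstract says safety is assessed primarily by adverse events, and the Statistical analysis section treats TSI as a further safety assessment. Adverse events, orthostatic symptoms and beat-to-beat blood pressure do not pass through this filter. That limits the consequence to the TSI component, though Table 1 does list that component under the primary safety outcome.

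**Conclusion.** The point holds for level and sustained response. Followed as written, the stated processing removes the TSI level exactly, and with it any tonic difference between baseline, active and sham. This follows from zero gain at 0 Hz and needs no assumption about sampling rate or filter order. It also removes about 83 to 100% of the 3-minute mean of a fall held through the stand. That range rests on the assumed filter type and sampling rate, and varies with order, phase and supine reference. It does not erase every TSI response to standing or stimulation. The risk is false reassurance, or a missed tonic benefit, when the mixed model is fitted to mean-level or sustained-response summaries. This is a stated processing rule that conflicts with the stated use of TSI, not a detail left to a fuller document.

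**What to change.** State in the Statistical analysis section that resting, active-stand and task-level TSI are analysed without the 0.01 Hz high-pass edge, using low-pass filtering and artefact removal only. Name the summaries that enter the models: for the stand, change from the supine pre-stand mean, as the nadir and as means over fixed post-stand windows; for the cognitive tasks, mean TSI level per task. Confine the 0.01–0.8 Hz bandpass to any separate haemoglobin or oscillation analysis, and say so.

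The cost is a sentence or two and one setting in the processing script. Filtering is done after recording, so data collection does not change. The drawback is that slow drift stays in the signal. For the stand, referencing each stand to its own supine baseline limits this; for mean level during the cognitive tasks that protection is not available in the same form, and the write-up should acknowledge it.
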